## Abstract

**Introduction:**

There is limited knowledge on how the SARS-CoV-2 affects pregnancy outcomes. Studies investigating the impact of COVID-19 in early pregnancy are scarce and information on long-term follow-up is lacking.

The purpose of this project is to study the impact of COVID-19 on pregnancy outcomes and long-term maternal and child health by: (1) establishing a database and biobank from pregnant women with COVID-19 and presumably non-infected women and their infants and (2) examining how women and their partners experience pregnancy, childbirth and early parenthood in the COVID-19 pandemic.

**Methods and analysis:**

This is a national, multicentre, prospective cohort study involving 27 Swedish maternity units accounting for over 86 000 deliveries/year. Pregnant women are included when they: (1) test positive for SARS-CoV-2 (COVID-19 group) or (2) are non-infected and seek healthcare at one of their routine antenatal visits (screening group). Blood, as well as other biological samples, are collected at different time points during and after pregnancy. Child health up to 4 years of age and parent experience of pregnancy, delivery, early parenthood, healthcare and society in general will be examined using web-based questionnaires based on validated instruments. Short- and long-term health outcomes will be collected from Swedish health registers and the parents’ experiences will be studied by performing qualitative interviews.

**Ethics and dissemination:**

Confidentiality aspects such as data encryption and storage comply with the General Data Protection Regulation and with ethical committee requirements. This study has been granted national ethical approval by the Swedish Ethical Review Authority (dnr 2020-02189 and amendments 2020-02848, 2020-05016, 2020-06696 and 2021-00870) and national biobank approval by the Biobank Väst (dnr B2000526:970). Results from the project will be published in peer-reviewed journals.

**Trial registration number:**

NCT04433364.

Strengths and limitations of this studyThe COVID-19 in Pregnancy and Early Childhood (COPE) study is a unique linkage between the Swedish Pregnancy Register, the Swedish Neonatal Quality Register, the Hospital Integrated Biobank Sweden and patient-reported outcomes through web-based questionnaires enabling both short-term and long-term follow-up of pregnant women, their partners and children during the COVID-19 pandemic.Prospective and automated collection of healthcare data in the comprehensive Swedish Pregnancy Register and Swedish Neonatal Quality Register covering more than 98% of all deliveries in Sweden ensures high-quality data.Logistics provided by Hospital Integrated Biobank Sweden enable high-quality biological sampling at several time points during pregnancy according to standardised protocols. However, due to resource limitations at the hospitals during the pandemic, some women will not have complete samples from all time points of interest.Based on validated instruments, child health and development during the first 4 years of life will be reported by parents along with comprehensive register-based long-term follow-up. There is a risk of selection bias regarding the follow-up questionnaires where we expect that a proportion of the study population will not answer the questionnaires.Other limitations include self-selection bias as women need to give consent to participate, and a prerequisite for participation in the interview part of the study is adequate Swedish or English language skills.

## Introduction

The emergence of a new coronavirus was brought to WHO’s attention on 31 December 2019. Within weeks, a global health emergency ensued and COVID-19 was declared a pandemic by the WHO. There was an urgent need to identify and protect vulnerable populations within the society and from the knowledge gained from the previous human coronavirus outbreaks of SARS-CoV-1 and Middle East respiratory syndrome CoV, it was clear that pregnant women and their fetuses may be particularly at risk for poor outcomes.^1 2^

### COVID-19 in pregnancy

Recent reviews have found that pregnant women are more likely to need intensive care treatment related to COVID-19 as compared with non-pregnant women.^3 4^ Increased severity of disease in late pregnancy along with rapid recovery after delivery has also been reported.^5–7^ Pregnant women with COVID-19 are often treated with low-molecular heparin due to a perceived increased risk of thromboembolic events but there is limited evidence.^8^ COVID-19 has been found to be associated with a higher prevalence of pre-eclampsia and preterm delivery.^4 9 10^ In addition, characteristics like advanced maternal age and high body mass index have been associated with an increased frequency of severe disease^4^ and there is insufficient knowledge on fetal malformations and miscarriages related to COVID-19 during early pregnancy. Current guidelines on how to monitor and treat pregnant women and their newborns are based on inadequate evidence with little data from infection in early or mid pregnancy.

### COVID-19 and the offspring

Transplacental transmission of SARS-CoV-2 remains a topic of much debate^11^ with several reports suggesting its possibility.^12^ Vivanti *et al*
13 and Zaigham *et al*
14 have reported convincing cases of vertical transmission but data on neonatal morbidity and neurodevelopment after SARS-CoV-2 infection during pregnancy are lacking. Although the majority of neonates born to SARS-CoV-2 positive mothers have reported mild, if any, symptoms, several studies have presented a spectrum of clinical symptoms, from mild to severe, in both SARS-CoV-2 positive and negative neonates.^15–18^ SARS-CoV-2 is a possible neurotropic virus, and it is well known that congenital or early neonatal infections with neurotropic viruses can impaire brain development.^19^ Further, infections in general during pregnancy and in the neonatal period are known to be associated with adverse consequences on brain development and neuropsychiatric diseases.^20 21^

### COVID-19 and childbirth/early parenthood experience

COVID-19 during pregnancy can have a profound impact on how a woman and her partner experience pregnancy, childbirth and early parenthood. The many unknowns connected to the virus have the potential to create anxiety in the pregnant population.^22^ International studies have indicated a possible rise in depression among pregnant and lactating women.^23^ There have been drastic changes in antenatal and delivery care routines in order to prevent the risk and spread of infection. These changes can have a profound effect on parents and newborns. Examples include limitations in allowing only the parent who gave birth to stay with the newborn at the postnatal ward, or that a newborn in need of neonatal care may be separated from the parents completely until they recover, resulting in the parents missing out on the important first days of bonding with their newborn.^24^

Similarly, severe maternal morbidity may aggravate emotional distress^25^ and may be linked to a higher risk of post-traumatic stress disorder in both the mother^26^ and the partner.^27^ This, in turn, may negatively influence the parent–infant bond and affect subsequent child development.

### Research premises in Sweden and rationale for the study

Antenatal care is offered free of cost for all women in Sweden and follows standardised guidelines.^28 29^ Research in Sweden offers the unique possibility to link data from national mandatory health registers, quality registers and registers held by the National Board of Health and Welfare with analyses on biological samples stored in Hospital Integrated Biobanks (SIB, http://www.biobanksverige.se/). Data retrievement and sampling by SIB and pre-established standardised registers with automatic transfer of data from medical records will not impact the workload of the ordinary hospital staff, and therefore, allow the study to proceed during the pandemic where there are already great constraints and limitations on healthcare resources. With almost universal smartphone usage in Sweden, patient-reported outcomes can be safely and efficiently collected using electronically distributed questionnaires.

In summary, uniformity in laboratory testing, use of hospital integrated biobanks with standardised protocols, follow-up of child health and parent-reported outcomes through survey data and linkage of data from national registers will improve knowledge on how COVID-19 can affect the mother, partner, fetus and child. Sweden is one of the few countries with preconditions that can enable an almost population-based follow-up on parent and child health despite the considerable strains imposed by the COVID-19 pandemic.

## Aims and objectives

The overall aim of this project is to study the impact of SARS-CoV-2 infection on maternal, fetal and child health, as well as experience of pregnancy and parenthood during the COVID-19 pandemic by:

Establishing a biobank with biosamples from both pregnant women with COVID-19 and presumably non-infected pregnant women and their infants.Establishing a database of survey-based data linked to Swedish quality and healthcare registers and information from electronic charts for both mother and child.Performing serological, viral and immunological analyses on biobank samples and linking these to maternal, fetal and child outcomes in order to assess short-term and long-term maternal and child health.Collecting prospective data on how women and their partners experience pregnancy, childbirth and early parenthood in the COVID-19 pandemic using validated questionnaires and qualitative interviews.

## Methods and analysis

### Study design and population

The COVID-19 in Pregnancy and Early Childhood (COPE) study is an ongoing Swedish multicentre study, facilitated by the Swedish network for national clinical studies in Obstetrics and Gynaecology (SNAKS, https://www.snaks.se/). Data are collected in four different ways: (1) biosampling, (2) survey-based follow-up until 4 years after delivery, (3) linkage to Swedish health and quality registers enabling long-term follow-up and (4) interviews. All Swedish maternity units with their corresponding neonatal care units have been invited to participate in the study. Centres can participate in the biobank and/or the questionnaire part of the study. So far, 27 maternity units corresponding to more than 87 000 of the approximately 114 000 deliveries per year in Sweden are participating in the study (online supplemental material 1).

10.1136/bmjopen-2021-049376.supp1Supplementary data

Patient recruitment formally started on 1 June 2020. All women, aged 18 years or older, receiving antenatal care or giving birth at participating centres are eligible for the study. Study information and questionnaires have been translated into the most commonly spoken languages in Sweden (Swedish, English, Arabic and Somali). A prerequisite for participation in the interview part of the study is adequate Swedish or English language skills.

Participants have access to study information which is freely available in the waiting rooms of the antenatal care and maternity units involved in the study, the COPE study homepage (www.copestudien.se), social media, interviews and articles available in mass media along with active recruitment by the local study research team.

Recruitment of pregnant women may occur at different time points during the pregnancy, for example, during the first or second trimester ultrasound screening visit, on admission for pregnancy complications or admission to the delivery/COVID-19 units of any of the participating hospitals.

Partners aged 18 years or older are also eligible for participation. Participating women and their partners receive oral and written information about the study and are required to provide written consent. Women can choose to participate in either the biobank or the questionnaire part of the study, or both.

The study is recruiting two groups of women and their partners: (1) a ‘COVID-19 group’ (figure 1A) and (2) a ‘screening group’ (figure 1B). The primary goal is to recruit 200 women in the ‘COVID-19 group’ and 1000 women in the ‘screening group’. Further recruitment to the biobank part will depend on adequate funding, study centre capacity and the overall progress of the pandemic. Inclusion to the questionnaire part of the study will continue until the obstetric and neonatal departments return to their prepandemic routines and social restrictions due to the COVID-19 pandemic are revoked.

**Figure 1 F1:**
[figure not shown]
(A) COVID-19 group: data and biospecimen collection overview. (B) Screening group: data and biospecimen collection overview. BSES, Breastfeeding Self-Efficacy Scale short form; CEQ, Childbirth Experience Questionnaire; COPE, COVID-19 in Pregnancy and Early Childhood; EPDS, Edinburgh Postnatal Depression Scale; EQ5D, EuroQol 5D; FTFQ, First Time Fathers Questionnaire; GSE, General Self-Efficacy scale; HADS, Hospital Anxiety and Depression Scale; SOC, Sense of Coherence Scale; SQ-PTSD, Screen Questionnaire-Post-Traumatic Stress Disorder; VAS, Visual Analogue Scale.

#### The COVID-19 group

This group includes women that (1) test-positive for SARS-CoV-2 during pregnancy or at delivery, (2) have a positive SARS-CoV-2 antibody test from infection during the current pregnancy or (3) have COVID-19 as a ‘clinical diagnose’ at the time point of delivery before test results are available.

Before June 2020, there was limited testing capacity in Sweden and only symptomatic patients admitted to the hospital were tested. Since June–July 2020, testing for SARS-CoV-2 has become widely available, even outside hospitals, to all citizens in Sweden. In the beginning of 2021, SARS-CoV-2 screening was introduced for all patients admitted to Swedish hospitals including pregnant women on admission to maternity units. All adults, including pregnant women, are currently required to take a SARS-CoV-2 test in case of symptoms. Detailed data on the number of performed tests and test-positivity in different regions, age groups and over time are available at the homepage of the Public Health Agency of Sweden.^30^ Due to restrictions on research-related appointments during the pandemic, women are recruited to the COVID-19 group when they seek inpatient care or in connection with their routine antenatal care visit. In the later case, they are included when they are in remission from COVID-19.

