#### The screening group

This group consists of women without symptoms and/or with a negative test for SARS-CoV-2 during the current pregnancy. These women are recruited at participating centres during their antenatal care check-up or during their visit to the maternity unit.

A woman in the screening group may be included into the COVID-19 group later on during the pregnancy if she contracts COVID-19. This may also be the case at the time of statistical analyses, in case the biobank specimens should indicate an asymptomatic SARS-CoV-2 infection or a positive test result is found registered in the Swedish Register for mandatory registration of notifiable infectious diseases (SmiNet).

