### Exposure definition in regard to clinical outcomes

Based on RT-PCR and serology and data from SmiNet, women will be divided into infected women (COVID-19 during pregnancy) and non-infected women (no COVID-19 during pregnancy). In some analyses/subanalyses, gestational age at infection, severity of disease, viral load and immune response will be considered as additional exposure variables for the infected group.

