### General statistical methodology

Demographics will be presented as numbers (percentage), medians or means as appropriate by distribution. Comparisons between groups will be analysed by Student’s t-test or Mann-Whitney U-test with means or medians and confidence intervals or IQR, as appropriate according to distribution of the variables. Categorical variables will be compared by χ^2^ test or Fisher’s exact test. Correlations will be analysed by Pearson’s r or Spearman’s r as appropriate by distribution of the variable. Regression analyses, unadjusted and adjusted, will be performed to adjust for known confounding variables. Ten cases per variable at the lowest will be considered appropriate to avoid overfitting of the model.

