## Discussion

Knowledge from previous coronavirus outbreaks^1 4^ has identified pregnant women as particularly susceptible to negative outcomes. While evidence is increasing on how SARS-CoV-2 infection in pregnancy can affect pregnancy outcomes,^9^ there is a need to thoroughly examine the burden of COVID-19 during the pregnancy with focus not only on the pregnant woman and the fetus but also the child after delivery and the pregnant woman’s partner. In addition, long-term consequences of COVID-19 during pregnancy are also relatively unknown.

Local and regional differences in the testing and management of pregnant women with SARS-CoV-2, make the results of published studies difficult to interpret. Many studies do not report the gestational age at infection, do not include a control group, recruit women only when they seek healthcare for obstetric complications or on admission for delivery, do not specify the indication for an obstetric intervention (intervention with or due to COVID-19) or are not generalisable since they are based on a single site with a population having a certain risk profile regarding, for example, socioeconomic status or pregnancy complications.^4^ It can, therefore, be argued that current guidelines on how to monitor and treat pregnant women and their neonates are based on inadequate evidence with little or no data on long-term follow-up.

Few studies have focused on women’s experience of pregnancy, childbirth and early parenthood during the COVID-19 pandemic and the results are often context specific, making them difficult to generalise. Partner experience has been largely overlooked^22^ and there is a lack of data on pregnancy and child outcomes secondary to SARS-CoV-2 infection in early pregnancy. Viral infections have been known to cause developmental problems for the fetus such as deafness (cytomegalovirus)^39^ or anaemia (parvovirus).^40^ Due to the novelty of SARS-CoV-2, the effect of the virus on fetuses in the first trimester is largely unknown.

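### Recruitment and testing can be triggered by an admission for a pregnancy complication, and the infected versus non-infected contrast neither orders infection before outcome nor accounts for recruitment setting

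*Protocol article*

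**What the plan says.** Under The COVID-19 group, the article states that "women are recruited to the COVID-19 group when they seek inpatient care or in connection with their routine antenatal care visit". The same section reports that in early 2021 "SARS-CoV-2 screening was introduced for all patients admitted to Swedish hospitals including pregnant women on admission to maternity units". A positive test during pregnancy or at delivery is enough to enter the group.

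Study design and population lists the points at which pregnant women may be recruited. Besides ultrasound visits these include "on admission for pregnancy complications or admission to the delivery/COVID-19 units of any of the participating hospitals". The list is not limited to one group.

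The screening group is described in two ways. In the abstract, its members "are non-infected and seek healthcare at one of their routine antenatal visits (screening group"). In The screening group, they are recruited "during their antenatal care check-up or during their visit to the maternity unit". No shares by setting are given for either group.

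For clinical outcomes, "women will be divided into infected women (COVID-19 during pregnancy) and non-infected women (no COVID-19 during pregnancy"), using RT-PCR, serology and SmiNet data. The additional exposure variables are gestational age at infection, severity, viral load and immune response. Under General statistical methodology, "Regression analyses, unadjusted and adjusted, will be performed to adjust for known confounding variables"; none is named.

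**The concern.** Entry to the infected group can be prompted by the outcome under study. A woman admitted with pre-eclampsia is tested because she was admitted. If positive, she can be recruited as a COVID-19 case although the outcome came first. A woman admitted with threatened preterm labour is in a similar position, with the outcome imminent rather than present.

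If non-infected women are recruited less often at such admissions, the infected group starts with more complicated pregnancies whatever the virus does. Adjustment for ordinary confounders such as age, BMI or parity does not remove this, because the distortion comes from how women enter and not from their characteristics. The outcomes at stake are pre-eclampsia and preterm delivery, and possibly SGA. The limitations in the strengths-and-limitations list and in the Discussion cover self-selection, language, drop-out and incomplete sampling, but not this.

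**Working it through.** **Inputs from the article (Sample size calculations and Table 3).** Target 200 COVID-19 and 1000 screening women; 10%–15% of the screening group assumed positive, giving more than 300 cases; 80% power, significance level 0.05; pre-eclampsia and preterm delivery both 6% versus 12% with 511/256 women; SGA 10% versus 20% with 199/199.

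**Table 3 first.** The two-proportion formula with pooled variance under the null, two-sided 0.05 and no continuity correction gives 511.0/255.5 for 6% versus 12% at 2:1, and 199.0 per group for 10% versus 20% at 1:1. The thrombosis row gives 612.8/306.4 (stated 613/306) and the neurological row 580.9/290.5 (stated 581/290). Table 3 reproduces and is not at fault.

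**Null mixture.** Let q be the share of a group entering on complication admissions, p_adm the outcome rate among those women, and 6% the rate among all others, with no COVID-19 effect:

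observed rate = 6% + q × (p_adm − 6%)

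Neither q nor p_adm is in the article; both are assumptions. The chance of p<0.05 is Φ[(p1 − p0 − 1.96 × SE0)/SE1], with SE0 from the pooled rate and SE1 from the separate rates.

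**Scenario: q = 25% of the 200 recruited COVID-19 women, p_adm = 30%.** The infected rate is 6% + 0.25 × 24% = 12%.

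| Comparison | Infected | Non-infected | Chance of p<0.05 |
|---|---|---|---|
| 200/1000, no screening admissions | 12% | 6% | 0.81 |
| 300/900, positives moved, no screening admissions | 10% | 6% | 0.64 |
| 200/1000, 5% screening share | 12% | 7.2% | 0.61 |
| 200/1000, 10% screening share | 12% | 8.4% | 0.38 |
| 200/1000, equal shares (25%) | 12% | 12% | 0.05 |

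- Row 1: SE0 = √(0.07 × 0.93 × (1/200 + 1/1000)) = 0.0198 and SE1 = 0.0242, so (0.06 − 0.0387)/0.0242 = 0.88 and Φ = 0.81.
- Row 2: 10% of 1000 gives 100 positives at 6%, so the infected rate is (50 × 30% + 250 × 6%)/300 = 10%. SE0 = 0.0170 and SE1 = 0.0190, so (0.04 − 0.0333)/0.0190 = 0.35 and Φ = 0.64.
- Row 4: 6% + 0.10 × 24% = 8.4%. SE0 = 0.0222 and SE1 = 0.0246, so (0.036 − 0.0434)/0.0246 = −0.30 and Φ = 0.38.

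**Range over the assumptions (200/1000, no screening admissions).** q = 10% at p_adm = 20% gives 7.4% and 0.13; q = 20% at 30% gives 10.8% and 0.66.

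**What a full doubling needs.** For 12% versus 6%, p_adm = 6% + 6%/q: 36%, 26% or 18% at q = 20%, 30% or 50%. For SGA at 20% versus 10%, p_adm = 10% + 10%/q: 60%, 43% or 30%. SGA therefore needs much higher rates among admitted women.

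**The case against.** **The asymmetry is not established.** The complication-admission sentence covers all pregnant women, and The screening group allows maternity-unit visits. A woman admitted with pre-eclampsia who tests negative could join the screening group. This stands: the documents do not show how far the two groups differ by setting, and with equal shares the bias is nil.

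**The analysed groups are not the recruited groups.** Positives found in the screening group move to the infected side, which dilutes the effect to 10% versus 6% in the scenario above. This also stands.

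**The Discussion does not convict the study.** A reader might infer that COPE repeats the fault it sees in others, namely studies that "recruit women only when they seek healthcare for obstetric complications or on admission for delivery". The word that matters there is *only*. COPE also recruits at routine visits, so it is better placed than those studies; what it shares with them is one recruitment route.

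**Covariates belong in the full plan.** The exact covariate list commonly does, and its absence here is not the point. The article itself fixes the recruitment routes, the testing on admission and the exposure contrast. Followed as written, these let an outcome that preceded the positive test count against infection.

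**Conclusion.** The mechanism is in the text and nothing in the article counters it: an admission can prompt both the test and recruitment, and the contrast uses neither the order of infection and outcome nor the recruitment setting. If complication admissions form a larger share of the infected group, pre-eclampsia, preterm delivery and possibly SGA are raised with no COVID-19 effect.

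The size is unknown. Under the assumed 25% share and 30% rate, the chance of a false positive runs from 0.81 through 0.64 and 0.38 down to the nominal 0.05, depending on whether screening positives are moved and how many screening women come from such admissions.

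A reader might infer that the comparison will produce Table 3's doubling, or that the bias is as large as the effect sought. The documents do not support either: 12% with 0.81 requires no screening women from complication admissions and no positives moved to the infected group. Nor does a doubling describe every row, since Table 3 assumes about 15-fold for thrombosis (2%/0.13%) and 4-fold for neurological disorders.

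**What to change.** For each pregnancy outcome:

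1. Count a woman as exposed only if her infection date (SmiNet, RT-PCR or serology) precedes the diagnosis of the outcome.
2. Exclude from the incident-outcome comparison women whose outcome was already present at first positive test or, for non-infected women, at inclusion.
3. Adjust for maternity unit and calendar testing period. The period before June 2020 precedes formal recruitment (1 June 2020), so it can classify infection dates only.
4. Report the comparison stratified by recruitment setting (routine visit versus inpatient or delivery), with the routine-visit stratum as a prespecified sensitivity analysis. Date order alone is not enough for preterm delivery, because a woman tested on admission for threatened preterm labour delivers after her test.

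Anchoring on infection date keeps women infected earlier and recruited at a later admission, and keeping inpatient recruits in the main comparison retains severe disease, which the plan treats as an exposure variable. SmiNet dates are already to be extracted. The article does not say that recruitment setting is recorded, so confirm this first.

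The cost is analysis-plan wording and precision. If half of the 200 were recruited on admission, power for 6% versus 12% in the routine-visit stratum is about 60% (100 versus 900), or about 80% (200 versus 900) if the roughly 100 screening-group positives are kept, against about 90% for the pooled 300 versus 900.
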